#### Screening

Study sites administered a grade-wide or school-wide screening questionnaire to assess adolescents’ exposure to violence and relationship status (two of the eligibility criteria noted above). For screening, sites used a variety of customized approaches based on their school protocols. All of the sites opted to include additional items on their screening questionnaires to learn more about the general health and well-being of 9^th^ or 10^th^ grade students (eg, “Do you have a primary doctor?” or “Do you eat fruits and vegetables daily?”).

#### Consent and Assent Process

Per California law, we sought active parental consent for study participation through either a signed copy of the consent form or verbal confirmation via telephone calls (by research staff) when there was a parent signature, but the permission checkmark was ambiguous. Consent forms were available in both English and Spanish. The consent process began in one of two ways: (1) either an in-class presentation about the study was delivered by an SBHC representative or (2) students who met the screening criteria were sent invitations through a required class at school to attend an informational event, where, if interested, they received more information about the study, and parental consent forms were distributed. A single high school differed from other sites in that it provided consent forms to students ahead of the screening procedure. Students were informed that they would receive a US $10 incentive for returning a parental consent form regardless of their parent's decision. They were directed to return parental consent forms to their respective SBHC.

For students whose parents provided study consent and met the screening criteria, site liaisons compiled an eligibility log with the following data: student’s last name, first name, and middle initial; student ID (optional); student’s sex assigned at birth; student’s reported gender identity; the number of screening criteria met (selected from a dropdown menu); school (selected from a dropdown menu); agency (selected from a dropdown menu); whether students have a sibling or step-sibling at the school; and whether that sibling participated in About Us in the past (criterion for exclusion). Evaluation data collectors (EDCs) used this log onsite to determine which students were fully eligible for the assent process.

The study’s EDCs administered the study assent process on the day of the baseline survey administration at a given site. At the time of assent, prospective participants of consenting parents who met all the other eligibility criteria and agreed to study participation were enrolled in the study.

### Baseline Data Collection

At the time of assent and prior to randomization, adolescents completed the baseline survey on a self-administered tablet device via the Qualtrics Offline Surveys application (version 1.4.06) [28]. Following survey administration, EDCs promptly uploaded responses to the QualtricsXM server as soon as a secure internet connection could be achieved. EDCs were provided Verizon Jetpack MiFi devices (7730L and 8800L) for this purpose.

Participants were enrolled and completed baseline surveys on a rolling basis during the spring and fall semesters of 2018 and 2019 and spring of 2020. The targeted enrollment was approximately 173 students per site over 5 semesters (34 to 35 students per semester) for a total of 865 students.

At the completion of baseline surveys for a given cohort at a given site, the EDCs submitted a baseline survey administration log to the evaluation project manager for review and transferred data to the evaluation statistician for randomization into either About Us (intervention) or standard of care (control).

Baseline data collection consisted of two separate instruments: a computer tablet-based survey designed to capture adolescent knowledge, attitudes, and experiences regarding sexual behavior, contraception, STI, and HIV/AIDS; and a brief survey that collected contact information for study follow-up purposes. EDCs were selected and trained by the evaluation team to represent the study in the local communities and schools within which About Us was being implemented and evaluated.

### Randomization

Following baseline survey completion, eligible adolescents who had already received parental consent and assented to study participation were randomized to either the intervention or control group.

To assign participants to study groups (intervention or control), we used a stratified permuted block randomization procedure to ensure balance in key covariates and experience factors across intervention conditions given our need to randomize in smaller cohorts within schools by semester (ie, blocks). Specifically, eligible and consented adolescents were subdivided into strata defined by the sex assigned at birth (male or female) and whether they had one or two of the screening experience factors, followed by permuted block randomization for each stratum. Within each stratum, participants were assigned to either the intervention or control group using a 60/40 split. The goal was to create a balance of sex assigned at birth and experience factors to ensure that the intervention and control groups had an equal distribution of these factors that may affect our primary outcome of interest (ie, having vaginal or anal sex without condoms). In other words, the stratification was done to avoid the potential imbalances or confounding due to the sex assigned at birth and the number of baseline experience factors.

Students randomized to the control group received business as usual (BAU) care only. Students assigned to the control group received no special services beyond BAU provided through the schools. To measure the control group experience, we included a set of general exposure items on the impact survey to assess self-reported dosage from or exposure to teen pregnancy programming or sex education during the study period in the school and community (eg, have you had a guest speaker come to your school to provide any of the following information: abstinence information, sexuality information, pregnancy prevention information, STI or HIV information, etc). We also collected data from our schools (on a “needs and resources assessment”) to evaluate content from BAU education during the study period using a brief, web-based survey collected from our site liaisons and the schools’ health education teachers.

Random assignment duties were limited to the study statistician and conducted within one week of baseline data collection at a particular study site. A participant’s random assignment to the intervention group was communicated to the evaluation project manager, who then transmitted this information to the respective SBHCs study site coordinators.

### Follow-up Data Collection

Follow-up surveys were administered at 2 separate time points following the completion of the About Us intervention (approximately 3 months and 9 months postprogram implementation). Similar to baseline data collection for cohort 1 (spring 2018), cohort 2 (fall 2018), and cohort 3 (spring 2019), most follow-up surveys were conducted in-person on school or SBHC grounds. Upon receipt of a signed assent form, adolescents completed the survey on a self-administered tablet device via the Qualtrics Offline Surveys application and in the presence of an EDC. For any adolescents who transferred or were absent, a follow-up contact protocol was used to locate and provide an opportunity to complete the survey. Specifically, using contact data provided by the adolescent at the baseline or 3-month survey, EDCs would undertake a series of contacts through email, text message, cell phone calls, home phone calls, and/or social media messaging, sending the adolescent a unique link to the follow-up survey. Adolescents received a US $10 incentive for each survey completed up to the end of March 2020.

Follow-up surveys for cohorts 4 and 5 were affected by the COVID-19 pandemic due to school closures and travel restrictions preventing evaluation staff from traveling to study sites to administer the surveys. As a result, the study team adopted an online follow-up protocol as the primary approach to administering follow-up surveys and increased the online survey incentive to US $25, as the literature shows this amount is more effective in increasing response rates [29].

Throughout the study and depending on whether the cohort was surveyed during the pandemic, it was possible for participants in both the intervention and control groups to receive incentives totaling as little as US $10 and as much as US $60. Survey incentives offered to all participants were different than program incentives offered only to those in the intervention group who completed About Us program sessions.

### Measures

Primary measures to be analyzed are listed below in Textbox 1. All secondary measures to be analyzed along with sources are provided in Multimedia Appendix 1 [30-36].

Behavioral outcomes used for the primary research question.**Outcome name:** Condomless vaginal or anal sex in the past 3 months (core measures for Personal Responsibility Education Innovative Strategies grantees) [36].
**Source item(s):**
When you had vaginal sex in the past 3 months, how often did you or a partner use a condom? Vaginal sex is when a penis is put in a vagina.When you had anal sex in the past 3 months, how often did you or a partner use a condom? Anal sex is when a penis is put in a rectum, ass, or butt.Original response options for vaginal or anal sex include 1 (all of the time), 2 (some of the time), or 3 (none of the time).
**Constructed measure:**
Construct a single, dichotomous outcome coded as 1 if the respondent indicated they had vaginal or anal sex without a condom in the past 3 months, 0 if they did not, or missing otherwise.To be recoded into a single dichotomous variable (vaginal or anal sex) with response options as follows: 0=all of the time (1), as well as participants who reported not having vaginal or anal sex in the past 3 months; 1=some (2) or none of the time (3); and (?)=missing response for vaginal or anal sex without a condom in the past 3 months.**Timing of measure:** 9 months following the completion of the program.

### Data Cleaning

#### Phase I

Data cleaning is being implemented in three phases. At the baseline, 3-month, and 9-month surveys, the evaluation team engages in a screening process beginning during data entry and using built-in checks for participant entries via Qualtrics. We are using predefined expectations about normal ranges (eg, aged 14 to 18 years), flagging of dubious data entry and patterns (eg, using prompts to confirm an entry), and skip patterns (eg, if students reported having been in a relationship, they received an additional branch of questions not given to those who never were in a relationship).

After retrieving Qualtrics data from each participant survey from the EDCs, project staff transfers the files to a password-protected shared drive. Participant data are transferred and warehoused in SPSS (version 27; IBM) by data wave (ie, baseline, 3 months, and 9 months). Using SPSS, we are recoding variables, creating new variables (eg, check-all variables, such as race and sexuality, recoded into one categorical variable), and labeling and formatting variables for analysis.

For each data wave and merged data sets, data are checked to ensure they meet predefined range expectations, logical skip patterns, and consistency checks and missing data patterns by examining variable descriptive summary statistics (eg, minimum, maximum, mean, median, and SD), frequency distributions, cross-tabulations, and graphical explorations of variable distributions (eg, box plots, histograms, and scatter plots). Data are also checked against expected data collections (based on the number of randomized participants, lags between baseline, and follow-up surveys) and errors in transferring data from Qualtrics (eg, duplicate entries and inadvertent deletions). This process is implemented using SPSS and SAS (version 9.4; SAS Institute).

#### Phase II

At this phase, we are going back to the original Qualtrics data files for any inconsistent data points and patterns to verify entries and add justifications for any changes made to the warehoused SPSS data.

#### Phase III

We will flag inconsistencies for further discussion and, if decisions are made to adjust reported values, those decision rules will be fully documented for reporting purposes. These rules will be informed by the literature, What Works Clearinghouse (WWC) standards, or best practice guidance. We will check for within-time point and across-time point inconsistencies and set up cleaning rules for both. For example, within a time point (eg, baseline), if a participant reports no history of anal sex but reports using a condom during anal sex in the last 3 months, both responses would be edited as missing values. Similarly, across time points (ie, baseline, 3-month, and 9-month assessments), if someone reports that they have never had anal sex at 9 months, but report having had anal sex at the 3-month evaluation, we will carry out two sensitivity analyses with (1) recoded 3-month data to match 9-month data and (2) recoded 9-month data to match 3-month data [37]. However, it is important to note that such inconsistencies are not expected due to the built-in skip patterns in our Qualtrics survey but are planned for nonetheless.

Additionally, any response values that were not supposed to have been provided based on built-in skip patterns will be recoded as “not applicable.” Overall, missing values will be differentiated with appropriate coding as “nonresponse,” “do not know,” and “not applicable” as needed, and some anomalies (if plausible) will be left unchanged (eg, true extreme values such as age at 18 years). Finally, original respondents’ data will be kept as a backup, and we will explore sensitivity analyses to check to what extent data cleaning edits influence our results, including the use of multiple imputation procedures described below.

### Primary Outcome

The primary outcome of this study is the impact of About Us relative to the standard of care 9 months following the end of the intervention on the prevalence of vaginal or anal sex without condoms in the past 3 months. Items specifically examine condom use during vaginal and anal sex independently (Textbox 1).

### Secondary Outcomes

The secondary outcomes are four-fold: 3 months and 9 months following the end of the intervention, what is the impact of About Us relative to the standard of care on (1) the prevalence of abstinence from vaginal or anal sex in the past 3 months, (2) composite scores of relationship communication and positive conflict resolution among participants involved in a relationship at baseline, (3) the prevalence of school-based health center service use or information receipt in the past 3 months, and (4) composite scores of condom use intentions and attitudes regarding condoms and other types of birth control? These secondary outcomes are summarized in Tables S1-S4 in Multimedia Appendix 1.

### Generalities of Statistical Analysis Methods

Statistical analysis will be undertaken using SPSS and SAS. All participants randomized to either intervention (About Us) or BAU will be included in the analyses using the intent-to-treat (ITT) principles. Our benchmark analysis data set will include all randomized participants with imputed data for missing covariate and outcome variables.

As part of our sensitivity analyses, two additional types of analyses will be implemented: modified intent-to-treat (modified ITT) and complete case analysis.

Modified ITT analysis (ie, analysis based on a data set that includes all randomized subjects who provide baseline measurements on primary and secondary outcomes and have at least one follow-up assessment) will also be implemented under different conditions for missing data adjustment (described below).

### Assessment of Baseline Equivalence

Equivalence between the intervention and control groups will be assessed for demographic characteristics and primary and secondary outcomes at 3 time points: baseline, 3-month, and 9-month follow-up. At the 3-month and 9-month time points, baseline characteristics and outcomes will be compared between participants who completed each assessment separately. For example, if 400 out of 533 randomized participants completed the 3-month assessment, their baseline characteristics and outcome measures will be compared between intervention and control group participants (n=400). The baseline equivalence results will be used to help identify issues such as a potential lack of equivalence due to attrition (study or program attrition). Baseline demographic characteristics and primary and secondary outcome measures that are statistically different between the treatment and control groups will be controlled in our primary and secondary outcome analyses as described below.

Demographic characteristics of interest include age, sex assigned at birth, and race and ethnicity. The mean age and its corresponding SD for intervention and control groups will be calculated. Frequencies and proportions will be produced for categorical outcomes such as sex assigned at birth and race and ethnicity. Race will be categorized into non-Hispanic White, non-Hispanic Black, Hispanic, and other races.

A Pearson’s Chi-square test (or Fisher’s exact test as needed) will be used to examine baseline differences between categorical variables (sex assigned at birth, race and ethnicity, primary and secondary outcomes, and group assignment at baseline, 3-month, and 9-month assessment time points separately.

A two-sample independent t-test (or a Mann-Whitney test, nonparametric test as needed) will be used to examine baseline differences between continuous variables (age and secondary outcomes) and group assignment at baseline, 3-month, and 9-month assessment time points separately.

Baseline equivalence analyses will be conducted using SAS, and statistical significance will be assessed at an alpha (Type I error) of 5%.

### Preliminary Data Analysis

Preliminary data analysis will involve routine range checks for continuous variables and frequencies and cross-tabulations for categorical variables. If necessary, continuous outcomes (eg, score-based measures) will be corrected using the least powerful transformations possible to meet our statistical modeling assumptions (ie, “normalize” univariate data that might be skewed or “straighten out” a bivariate curvilinear relationship) of outcome and covariate relationships for linear regression [38]. In addition, bivariate analyses will be performed to identify potential nonlinear relationships (eg, between 9-month continuous outcomes and baseline characteristics and measures such as age and composite scores) that may need to be modeled. Preliminary analysis of score-based (or instrument-based) outcomes will include examining evidence of construct validity and reliability. Construct validity refers to the degree to which an instrument or measure assesses the underlying theoretical construct it is supposed to measure (ie, the test is measuring what it is purported to measure). This will be examined via confirmatory factor analysis for score-based outcomes. Reliability refers to the degree of interrelationship or homogeneity among question items on a test (questionnaire), such that they are consistent with one another and measure the same construct; this will be examined by generating an internal consistency index–Cronbach’s alpha for our score-based outcomes.

### Statistical Analysis Models

For dichotomous outcomes at 9 months, we will use logistic regression models with covariates (see Textbox 2) for the intervention, baseline outcome variables, strata variables (sex assigned at birth and number of screening experience factors present), sociodemographic characteristics (age and race and ethnicity), the time elapsed between baseline and the follow-up survey (at 3-month and 9-month follow-up), cohort, and school. For continuous outcomes, we will use linear regression models with covariates for the intervention, baseline outcome variables, strata variables (sex and number of screening risk factors present), sociodemographic characteristics (age and race and ethnicity), the time elapsed between baseline and follow-up surveys (at 3-month and 9-month follow-up), cohort, and school. Additional (exploratory) analyses will test for 3-way and 2-way statistical interactions and adjust for prognostic factors such as potential confounders of intervention effects. Similarly, we will include a covariate that captures whether our outcome data were collected pre-COVID-19 versus during the COVID-19 pandemic. Potential 2-way interactions involving this covariate and intervention group, age and grade, and relationship status will be examined to test the differential effects of the pandemic on outcomes of interest.

Covariates included in impact analyses.**Screening factor:** one or two screening factors present (categorical variable).**Age (years):** baseline date to DOB (continuous variable).**Sex:** sex assigned at birth; 1=male, 2=female (dichotomous variable).**Race and ethnicity:** White, Black, Hispanic, other (categorical variable).**Number of days between baseline and the follow-up survey (3 or 9 months):** follow-up date to baseline date (continuous variable).**Cohort:** cohort 1 (spring 2018), cohort 2 (fall 2018), cohort 3 (spring 2019), cohort 4 (fall 2019), and cohort 5 (spring 2020; categorical variable).**School:** high schools 1 to 7.

We will also take advantage of all measurement time point data and appropriately model the data hierarchy by exploring the use of generalized linear mixed models (GLMM) [39,40] to evaluate intervention effectiveness. The GLMM will allow us to use all data available and adjust for multilevel dependencies (eg, repeated measures, such as baseline and follow-up at 3 months and 9 months, within an individual participant nested within the intervention or control group, within a cohort (block) and study site). Additional analyses to account for multilevel effects will be explored as secondary or sensitivity analyses.

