### Intervention

Developed from a piloted intervention, About Us is an innovative healthy relationships intervention that promotes positive adolescent romantic relationships, condom use, and highly effective contraceptives if participants are having sex. The program includes 10 lessons (2 lessons are 30-45 minutes long and 8 are 50 minutes long) that blend group-based activities with online activities implemented in a small group format with students in grades 9 or 10 who have parental consent and provide assent to participate.

About Us draws on the latest research on developmental neuroscience to shape content and strategies. Part of the innovative design of About Us stems from the use of positive youth development (PYD) principles and adolescent development literature as core elements that are foundational to the curriculum. PYD is a strength-based approach used to promote adolescents’ prosocial competencies and skill-building related to their positive health and well-being [22]. The adolescent development literature, such as that reported by Collins [23], guides the relationship development content and helps ensure it is age-appropriate.

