### Recruitment

#### Power Analyses

For a statistical power of 80%, to detect a 9% difference (effect size: prevalence ratio=0.74, 95% CI 0.60-0.91 equivalent to an odds ratio [OR] of 0.65 or Cohen’s *d*=0.24) in the prevalence of condomless sex at 9 months between intervention and control group participants with an allocation ratio of 3:2, we needed to have a sample size of 508 and 339 subjects in the intervention and control groups, respectively, based on a simple two-tailed proportion difference test at a Type I error of 5%.

We selected a minimum detectable effect of Cohen’s *d*=0.2. The rationale for this selection is two-fold: (1) in our R21 pilot test of a less robust version of the About Us curriculum with a very small (<100) sample, we achieved an estimated effect size of *d*=0.15 for our unprotected sex outcome, and (2) in a meta-analysis of group-based pregnancy or STI interventions, the average effect size across multiple studies was OR 0.70, which corresponds to a small Cohen’s *d*=0.19 [26,27].

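### Small-group delivery in the intervention arm only is left out of the benchmark regressions and the power calculation, so if outcomes correlate within groups the standard errors are too small and type I error exceeds 5%

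*Protocol article*

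**What the plan says.** The Intervention section of the protocol article describes a programme "implemented in a small group format with students in grades 9 or 10". Health educators from the school-based health centers lead the group sessions, and students assigned to treatment attend them. Under Randomization, students are allocated individually within strata, and controls receive business as usual only.

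The benchmark analysis is in Statistical Analysis Models: "For dichotomous outcomes at 9 months, we will use logistic regression models with covariates". The covariates are intervention, baseline outcome, strata variables, age, race and ethnicity, elapsed time, cohort and school. Continuous outcomes get the matching linear model. Presentation of Categorical Outcomes promises a Wald confidence interval for the odds ratio.

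The same section then proposes exploring generalized linear mixed models with participants nested in arm, cohort and site. It gives this work a subordinate status: "Additional analyses to account for multilevel effects will be explored as secondary or sensitivity analyses". The two analyses named under Sensitivity Analysis reuse the benchmark regressions and change only the missing-data handling and the analysis set.

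The sample size in Power Analyses is "based on a simple two-tailed proportion difference test at a Type I error of 5" per cent.

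**The concern.** Students are randomised one by one, but one arm is then put into groups: a partially nested design. Intervention students in a group share peers, a facilitator and discussion over 10 sessions, and controls share nothing comparable. If that shared experience makes outcomes more alike within groups, the intervention-arm mean varies more than independent observations would imply.

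The school and cohort covariates shift both arms together, so they do not remove variance present in one arm only. The benchmark interval for the primary outcome would then be too narrow and its p-value too small, and the stated power would omit the same variance.

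**Working it through.** **1. The plan's own figure.** Power Analyses gives these inputs: "For a statistical power of 80%, to detect a 9% difference", "prevalence ratio=0.74, 95% CI 0.60-0.91 equivalent to an odds ratio [OR] of 0.65", and "with an allocation ratio of 3:2". A 9-point difference with a prevalence ratio of 0.74 implies a control prevalence of 0.09/0.26 = 34.6% and an intervention prevalence of 25.6%. With the pooled-variance two-proportion formula, two-sided 5% and no continuity correction:
- 34.6% v 25.6% gives 337 controls and 506 intervention students.
- Rounded to 35% v 26%, it gives 339 and 508.5.

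The second result matches the article ("we needed to have a sample size of 508 and 339 subjects in the intervention and control groups"). The figure therefore rests on independent observations and holds no allowance for clustering.

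**2. Assumptions the article does not supply.**
- Group size m. One group per site and semester would be 7 × 5 = 35 groups. As enrolled, 316/35 ≈ 9; as planned, 508/35 ≈ 14.5.
- ICC within delivery groups: 0.01 to 0.05, with 0 and 0.10 as outer values.

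**3. Formulas.**
- Design effect, intervention arm only: DE = 1 + (m − 1) × ICC.
- Ratio of true to naive standard error: R = √[(DE/316 + 1/217) / (1/316 + 1/217)].
- Actual two-sided type I error: 2 × Φ(−1.96/R).

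**4. Results at the enrolled 316/217, m = 9.**

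| ICC | DE | R | Type I error |
|---|---|---|---|
| 0 | 1.00 | 1.000 | 5.0% |
| 0.01 | 1.08 | 1.016 | 5.4% |
| 0.02 | 1.16 | 1.032 | 5.8% |
| 0.05 | 1.40 | 1.078 | 6.9% |
| 0.10 | 1.80 | 1.151 | 8.9% |

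Example, ICC 0.05: (1.40 × 0.003165 + 0.004608)/(0.003165 + 0.004608) = 1.163, whose square root is 1.078; 1.96/1.078 = 1.818, giving 6.9%.

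For ICC 0.01 to 0.05, groups of 6 give 5.2% to 6.2% and groups of 12 give 5.5% to 7.7%.

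**5. Do the school and cohort effects remove it?** A simulation (3,000 runs per scenario, 316/217, m = 9) fitted logistic regression with school and cohort fixed effects to data clustered in the intervention arm only. Rejection rates were 4.9% (ICC 0), 5.7% (0.02), 7.5% (0.05) and 9.3% (0.10), with Monte Carlo error of about 0.4 to 0.6 points. They do not remove it.

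**6. Planned power at 508/339, m = 14.5.** With DE applied to the intervention-arm variance and prevalences of 34.6% v 25.6%, power falls from 80% to 78% (ICC 0.01, DE 1.135), 76% (ICC 0.02, DE 1.27) and 71% (ICC 0.05, DE 1.675).

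**The case against.** The strongest reply is that the size is unknown and may be nil. The article gives no ICC and no group size. If the programme and its groups affect nobody, individual randomisation creates no intervention-only clustering, because likeness among schoolmates is then common to both arms. The inflation arises when groups do influence outcomes but the influences average to zero. This stands, and it is why the point is conditional.

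Second, the authors saw the hierarchy. If each site ran one group per semester, arm within cohort and site identifies the delivery group, so the proposed mixed model might come close to it. The group sizes used above rest on the same premise, so it would be unfair to say that model cannot capture the group. What remains is its status: it is exploratory and does not govern the benchmark test.

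Third, a Wald interval can use a robust variance, and a condensed article may leave the estimator to the analysis plan. That is possible. But the article does fix the benchmark model, and it assigns multilevel adjustment to secondary or sensitivity work.

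Fourth, clustering may be weaker than assumed. The Limitations section says that some recruits never received the programme, attrition shrinks the observed groups, and baseline adjustment can lower the residual ICC. All of this pulls the figures down.

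Finally, under-enrolment is the larger loss of power. At 316/217, before attrition, power for the planned effect is about 61% without clustering and about 55% with m = 9 and ICC 0.05. The power remark therefore corrects a statement and cannot change the sample.

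**Conclusion.** The point holds conditionally. The structure is certain: one arm is grouped, the benchmark models name nothing for the group, and the power figure assumes independence. The size is an assumption: a true standard error 1.6% to 7.8% larger and type I error of about 5.4% to 6.9% for groups of 9 and ICC 0.01 to 0.05, 8.9% at ICC 0.10, and none at ICC 0.

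A reader might infer two stronger things that the document does not support. One is that type I error definitely exceeds 5%; that needs positive within-group correlation, which the article neither states nor rules out. The other is that the error favours the intervention. The tests are two-tailed, and an interval that is too narrow overstates the evidence equally in both directions.

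The change is still worth making, because it concerns the benchmark test of the primary outcome and the named sensitivity analyses would not reveal the problem.

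**What to change.** - **Benchmark models.** Account for delivery group in the intervention arm, with each control as its own cluster. Cluster-robust standard errors with a small-sample correction are preferable because they keep the marginal odds ratio. The alternative is a random intercept for group in that arm only, which makes the odds ratio conditional on group.
- **Students who never joined a group.** Keep them in the intervention arm and treat each as a singleton.
- **Imputation.** Apply the adjustment in each imputed data set and reflect delivery group in the intervention-arm imputation model. Handling Missing Data already imputes the arms separately, so there is a natural place for it. Imputing without the group would pull the estimated within-group correlation towards zero.
- **Power statement.** Say that 80% power at 508/339 assumes no within-group correlation, and give the range of about 78% to 71% with its assumed ICC and group size.

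The cost is slightly wider confidence intervals and a little more modelling, mainly in the imputation step. It also needs a record of which group each intervention student attended, which programme delivery should provide.
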